### Recruitment {15}

#### Recruitment and retention plan

Patients will be recruited from participating FQHCs using a variety of recruitment strategies the PI has used successfully in her prior research at FQHCs (e.g., identification by EMR, patient flyers, working with clinic staff members and providers). Patient recruitment during the first 4 years of the study will proceed as follows (Fig. 2):A web interface through EMR links patient information and scheduling information at the time of each encounter form generation. EMR queries the preloaded databases and/or registries to determine if there is a match for the study, based on diagnosis codes (ICD 10- E08.00).At the visit to the primary practice where diabetes is on the problem list, EMR will flag the patient chart and indicate that the patient is eligible for the study. The practice staff will inform the patient about the study and direct the patient if interested to the research assistant (RA) for more information regarding the study. If the RA is not available, the practice staff will give the permission to call (PTC) form to interested patients to complete and sign for RA to pick up.A patient’s primary care physician (PCP) can identify patients as having diabetes by adding Diabetic codes to their EMR problem list.Patients that sign the PTC Form will be contacted by the RA either in the office or over the phone. The RA will briefly describe the project to the patient and if he/she is interested to participate, he/she will be scheduled for a group visit. The consent and HIPAA forms will be completed during the group visit. The RA or PI is responsible for answering questions and explaining the consent. Practice personnel will not be involved in obtaining consent.The patient may consent to the study, including follow-up, or may decline. At the time of consenting, the patient will be asked for several ways they can be contacted for follow-up. The practice will retain one copy of the consent, one will be forwarded to data entry (see below) and then to the RA who will retain it in the study files, and a copy will be given to the patient. The patient’s response to the enrollment offer will be entered into EMR as their consent form version (consent declined, or consent). If the patient declines to consent to the study, the patient will follow up with their physician as usual.Patients in clinics/teams randomized to group 1 will experience the patient activation intervention (Office-GAP) + medication adherence and life-style promotion intervention via Short Message Service on their cell phone (Way2Health).Patients in clinics randomized to group 2 will only receive medication adherence and life-style promotion intervention via Short Message Service on their cell phone (Way2Health).

**Fig. 2 Fig2:**
[figure not shown]
Patient flow

## Assignment of interventions: allocation

### Sequence generation {16a}

#### Randomization

We chose team-level assignment to unify all providers and patients at a team into a single intervention, minimizing risk of contamination. Seventeen teams from 12 clinics in 3 counties (with 4, 7, and 6 teams, respectively) agreed to participate in the trial. We first generated a uniformly distributed random variable (U) using a pseudo-random number generator in Stata and each team was allocated a random number. Then we stratified the teams by county, and the randomization procedure within each county followed these steps. In the county that had 1 team per clinic, the teams were sorted by U and the first half of the teams were assigned for group 1 and the second half for group 2. In the county that had 3 clinics with 2 teams and 1 clinic with 1 team, we sorted the teams within each clinic by their U values and in the 2-team clinics the first one was assigned to group 1 and the other to group 2; and the single-team clinic was randomly assigned to group 1 because U was less than 0.5 (which is a predetermined rule for assignment). Finally in the county with 3 teams in 1 clinic and 1 team in 1 clinic, all teams were sorted by U and the first 2 teams were assigned to group 1 and the last 2 teams were assigned to group 2. Overall, 9 teams were assigned to group 1 and 8 to group 2.

We chose this approach because it is realistic for providers and patients. This also helps the comparison of control and intervention groups to be more accurate because there is less chance of mixing between the two groups. In Michigan, FQHCs have similar numbers and types of providers (internal medicine, and family medicine) and nurse practitioners.

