Hence the net difference (DID) at 12 month is *β*_32_. Our study is powered to test the hypotheses: (a) *H*_0_ : *β*_31_ = 0, (b) *H*_0_ : *β*_32_ = 0and jointly (c) *H*_0_ : (*β*_31_, *β*_32_) = 0. Two other design features are a serial correlation *ρ*_*W*_ between repeated measures over time, an intra-class correlation (ICC) *ρ* for clustering within practice team. We obtained plausible inputs for *r* and *ρ* from the literature and our own experiences [45–48]. In community intervention studies *ρ* is small (we use 0.002) but *ρ*_*W*_ is much larger (we use 0.30). The hypothesized adherence rates at 0, 6, and 12 months are 0.40, 0.42, and 0.42 in group 2 and projected to be 0.40, 0.62, and 0.65 in group 1. With 9 teams in the combined intervention group, 8 in the text alone group, and at least 22 patients in each team, the power to detect differences between groups at 6 months and 12 months is 80.8% and 90.4%, respectively. The power to detect the DID at 6 months is 71.4% and 83.1% at 12 months. Thus, our target sample size is a total of 320 patients. Because some attrition is expected over the 4-year period, we will recruit a total of 378 patients to account for attrition of 10% in YR=1, another 4% in YR=2, and another 2% in YR=3.

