## Statistical methods

### Statistical methods for primary and secondary outcomes {20a}

#### Statistical analysis

Medication adherence will be assessed in individual patients by eCAP monitoring. Hypotheses will be tested at 6 months and 12 months.Tests are two-tailed at 5% level of significance. We compare group 1 patients to group 2 patients at baseline using, as appropriate, ANOVA-F-tests, chi-square tests, and non-parametric tests to assess equivalence of potentially confounding physiological and contextual patient characteristics. If substantive differences are found, they will be adjusted for in subsequent analyses by regression techniques, guided by the degree of dissimilarity rather than strict statistical significance [63]. Equivalence between the groups will be assessed on age, gender, education, race/ethnicity, use of statins, b-blockers, aspirin, and ACE1/ARB, blood sugar and lipid values, and team factors such physician experience.

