##### Analysis of the primary and secondary outcomes

We adopt a regression-based approach to multivariable modeling that incorporates features of clustering of patients within the practice team and correlation over time in repeated assessments. Repeated measures ANOVA, or more apropos, generalized linear (mixed) models (GLMM) will be used [64]. Generally, outcomes are assessed at baseline and at 2 additional time-points 6 months and 12 months. By choice of link function connecting the expected patient outcome to covariates, GLMM can be applied to different types of outcomes (continuous, categorical, count, ordinal). They can incorporate random effects to capture serial correlation within patient measures, and clustering of patients within practice teams. Covariates are patient characteristics, some of which are time-invariant such as the aforementioned sociodemographic variables, and characteristics of the practice team. Key right-hand side variables in addition to the covariates are a single indicator for group, with control as referent, two indicators for time, with baseline as referent and group by time interactions. The GLMM allows us to formulate and test hypotheses on functions of the regression parameters: they include (i) point-in-time comparison between group 1 and group 2, (ii) time-averaged comparison between group 1 and group 2, (iii) within group comparison for change over time, and (iv) change in group 1 compared to the corresponding change in group 2 via difference-in-differences (DID). SAS Software (ver 9.4, Analytics 15.1 or higher) will be used for statistical analyses.

##### Analysis of the exploratory outcomes in Aim 3

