##### Patient Activation Measure (PAM)

PAM is a continuous score on a 0–100 scale. Higher scores are associated with better activation [71, 72]. For MAI as continuous response, the beta regression model [73] with logit link posits the conditional mean and variance where *f*<1 is the under-dispersion. For PAM as continuous response, we will use a linear mixed model with mean and variance. Methods for the UKPDS risk score and patient engagement are entirely analogous. The structural forms of and are elicited from preliminary analyses of residuals [64]. Estimation of model parameters is via full maximum likelihood (ML), quasi-ML or restricted ML [64].

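### County, the randomisation stratum, is not named in the analysis model, covariates follow observed baseline differences, and full ML is left open with only 9 v 8 teams

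*Protocol article*

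**What the plan says.** **Randomisation.** Under Sequence generation {16a}, 17 teams in 12 clinics and three counties (4, 7 and 6 teams) were allocated: "Then we stratified the teams by county, and the randomization procedure within each county followed these steps". In the seven-team county, three clinics had two teams each, and one team of each pair went to each arm.

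**Model.** The Sample size section sets out a minimal linear predictor. The section Analysis of the primary and secondary outcomes repeats it, giving the key terms as "a single indicator for group, with control as referent, two indicators for time, with baseline as referent and group by time interactions". To these it adds patient characteristics, characteristics of the practice team, and random effects for repeated measures within patients and for patients within teams. Neither section names county, clinic or a team-by-time effect.

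**Covariates.** The Statistical analysis section compares the arms at baseline and continues: "If substantive differences are found, they will be adjusted for in subsequent analyses by regression techniques". The choice is to be guided by how dissimilar the arms look. The list to be compared includes physician experience as a team factor, but no randomisation stratum.

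**Estimation and testing.** Under the Patient Activation Measure heading: "Estimation of model parameters is via full maximum likelihood (ML), quasi-ML or restricted ML". On testing: "Tests are two-tailed at 5% level of significance". No reference distribution or degrees-of-freedom method is given.

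**Size.** "With 9 teams in the combined intervention group, 8 in the text alone group, and at least 22 patients in each team"; the evaluable target is 320 patients, and the team ICC used is 0.002.

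**The concern.** An analysis should reflect the restrictions placed on the randomisation. Stratifying by county balances the counties across the arms. If county explains part of the difference between teams, a model without it leaves that part in the error term, and the reported standard error is larger than the design earned.

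A different issue is the small number of teams. Full ML divides the team-level sum of squares by 17, not by 15. With a normal reference distribution, that gives a test that rejects too often.

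The primary hypotheses are difference-in-differences (DIDs) at 6 and 12 months. In a linear model a random team intercept cancels from a change, so it gives the DID standard error no protection if team effects drift over the year.

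Finally, choosing covariates after seeing baseline differences leaves the adjustment set for the primary contrast open until the data are in. That matters in an open-label trial.

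**Working it through.** **1. Allocation, reproduced from the Randomization section**

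| County | Clinics | Teams | Group 1 v group 2 |
|---|---|---|---|
| One three-team clinic and one single-team clinic | 2 | 4 | 2 v 2 |
| Three two-team clinics and one single-team clinic | 4 | 7 | 4 v 3 |
| One team per clinic | 6 | 6 | 3 v 3 |
| Total | 12 | 17 | 9 v 8 |

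This agrees with the protocol. Eight of the 12 clinics (1 + 1 + 6) have a single team. With 320 evaluable patients, team size is 320/17 = 18.8; 19 is used below except in step 4.

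**2. Precision lost by omitting county**

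Let s be the share of between-team variance that lies between counties (assumed). The variance of a team mean with county in the model, relative to without it, is [ICC(1 − s) + (1 − ICC)/m] / [ICC + (1 − ICC)/m].

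Example, ICC 0.02 and s = 0.25: (0.0150 + 0.0516)/(0.0200 + 0.0516) = 0.93.

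| ICC | s = 0.25 | s = 0.50 |
|---|---|---|
| 0.002 (protocol) | 0.99 | 0.98 |
| 0.02 (assumed) | 0.93 | 0.86 |
| 0.045 (assumed) | 0.88 | 0.76 |

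Adjustment therefore cuts the variance by 7 to 24% over the assumed range. Put the other way, omission makes it 1/0.93 to 1/0.76, or about 8 to 31%, larger. This is before the cost of moving from 15 to 13 df: (2.160/2.131)² = 1.03.

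A simulation under the actual allocation scheme agrees in direction. At ICC 0.05 the mean reported SE was 0.149 without and 0.134 with county terms when county carried 50% and clinic 30% of team variance, and 0.155 in both cases when they carried none. At ICC 0.002 it was 0.120 v 0.121.

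**3. Type I error of the point-in-time test**

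Setting: 17 teams of 19, continuous outcome, no county or clinic variance, 400,000 simulated trials per row.

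| ICC | ML, z | REML, z | REML, t on 15 df |
|---|---|---|---|
| 0.002 | 4.8% | 4.3% | 2.8% |
| 0.01 | 5.8% | 5.1% | 3.4% |
| 0.02 | 6.7% | 5.8% | 4.0% |
| 0.03 | 7.4% | 6.2% | 4.3% |
| 0.045 | 8.0% | 6.6% | 4.7% |

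The limit for ML with z, when the team variance estimate is positive, is 2·P(t₁₅ > 1.96·√(15/17)) = 8.5%. With two county terms added and ML with z retained it is 2·P(t₁₃ > 1.96·√(13/17)) = 11.0%.

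When county and clinic carried 80% of the team variance and were omitted, ML with z gave 3.9 to 4.6% over ICC 0.002 to 0.10. Omitting strata that matter therefore lowers the error rate.

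**4. DID with no team-by-time effect**

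With serial correlation 0.30 (protocol), the patient-level change has variance 2(1 − 0.30) = 1.4 times the patient variance. If team effects correlate at c over time (assumed), the true variance exceeds the modelled one by 1 + 2·ICC·(1 − c)/[(1 − ICC)·1.4/18.8].

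| ICC | c = 0.8 | c = 0.5 |
|---|---|---|
| 0.002 | 1.01, error 5.1% | 1.03, error 5.3% |
| 0.02 | 1.11, error 6.3% | 1.27, error 8.2% |
| 0.045 | 1.25, error 8.0% | 1.63, error 12.5% |

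**5. Do the stated powers reveal a larger ICC?**

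No. At N = 320 and ICC 0.002, standard formulas give 94.3% and 98.4% for the point-in-time tests and 85.7% and 93.8% for the DIDs, against the stated 80.8%, 90.4%, 71.4% and 83.1%. An ICC near 0.03 comes within about two points of all four. At ICC 0.045 and N = 374 the two point-in-time figures fit (80.7%, 90.6%) but the DIDs do not (66.6%, 78.7%). The powers do not identify an ICC, so every value above 0.002 here is an assumption.

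**The case against.** A reader might infer that the protocol commits to large-sample inference and that its tests will exceed 5%. The document does not support that. It states no z or Wald test, REML is one of its three options, and the degrees-of-freedom rule is commonly left to the SAP. Only a conditional statement stands: ML is left open, and with large-sample tests it would be liberal once the ICC reaches about 0.01.

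A reader might also link the missing county term to false positives. The link runs the other way, since omitting informative strata is conservative.

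Nor is county excluded. The predictor is introduced as a minimum, and team characteristics are allowed as covariates. Likewise, the random effects are written as a general vector whose form is to be informed by residuals, so a team-by-time effect is unnamed but not ruled out. Both points stand. The gap is that nothing commits the analysis to either term.

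At the protocol's ICC of 0.002 there is no material harm of any kind; this stands in full. The calculations also use a balanced continuous outcome, whereas adherence is to be fitted by beta regression with a proxy baseline, so the sizes are approximate.

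A random clinic effect would be poorly identified, because only four of the 12 clinics have more than one team. This stands and shapes the fix.

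**Conclusion.** The point holds as a mismatch between design and analysis. Teams were randomised within county, and within clinic for three pairs. The stated model names neither, ties other covariates to observed baseline differences, and leaves the estimator open with 17 teams.

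The effects are separate:

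- Omitting county loses precision if county matters. The variance would be 7 to 24% smaller with it, under ICC 0.02 to 0.045 and a county share of 25 to 50%.
- ML with large-sample tests, if used, would give about 6 to 8% type I error at ICC 0.01 to 0.045.
- A DID model without team-by-time variation would understate its standard error if team effects drift: 6.3 to 12.5% error at ICC 0.02 to 0.045 and a correlation over time of 0.8 to 0.5.

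The ICCs, county shares and correlations of team effects are assumptions. At ICC 0.002 all three effects are negligible. The change is worth making because it is cheap and removes discretion over the primary p-value, not because an error rate above 5% has been shown.

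**What to change.** Make these changes together, before analysis:

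- Add county as a fixed effect. Handle the pairing within the three two-team clinics in a sensitivity analysis, or by a randomisation test that follows the allocation scheme, instead of a random clinic effect in the main model.
- Name the other covariates in advance instead of selecting them on baseline differences.
- Include a team-by-time random effect in the model for the DID contrasts.
- Specify REML (linear models) or residual pseudo-likelihood (generalised models) with Kenward-Roger or between-team degrees of freedom.

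Do not add county while keeping ML with a z test: that raises the limiting type I error from 8.5% to 11.0%.

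Cost: a few sentences in the analysis plan and the matching code, two team-level degrees of freedom (15 to 13), and a team-by-time variance that 17 teams may estimate weakly. If the ICC really is near 0.002, between-team degrees of freedom also make the test conservative (2.8% in the point-in-time simulation).

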### Concealment mechanism {16b}

We do not randomize patients; we randomize clinics. Allocation is concealed during recruitment. We reveal to both patients and providers which arm the clinic has been randomly assigned to once they give consent to participate.

### Implementation {16c}

The statistician generated the allocation sequence, and all clinical staff were notified prior to enrolling patients. Because this is a cluster randomized trial, all patients at a particular team will be in the same arm. Patients are enrolled by the RA assigned to each clinic after signing the informed consent agreement.

## Assignment of interventions: blinding

### Who will be blinded? {17a}

After the 17 teams are randomly assigned to the two arms, neither trial participants nor the care providers can be blinded to the assignment due to the nature of the intervention. Neither the participants nor the researchers are blinded for this study.

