##### Office-GAP follow-up visit with providers

The Office-GAP Checklist is the core tool of our SDM intervention. A one-page checklist, this SDM tool outlines all evidence-based medications for secondary prevention of CVD in T2DM patients. It is an in-consultation decision support tool that helps engage the patient and provider to encourage and enhance an SDM process via discussion of medication and secondary prevention/lifestyle changes during an office visit. In this study, the Office-GAP Checklist will be completed by the physician with direct patient involvement during the office visits at 0–1, 3, 6, 9, and 12 months. Only group 1 patients will use this checklist during their office visits.

The Office-GAP Checklist also serves as a physician reminder at the point of care, because the physician records a checkmark for each medication: “Yes” (if patient is on the medication), “No” (if patient is not), or “Does not apply to me because….” A reason for exclusion of a medication is also provided (patient is not eligible for the medication, has a contraindication to its use, or the patient and physician have identified an alternative due to side effect or cost concerns). Details about the next appointment and any secondary prevention plan changes are also listed on the form. At the end of the visit, both patient and physician sign the form to confirm that they have reviewed the checklist. The patient receives a copy of the checklist to take home and a copy is retained in the patient record. All providers in the intervention teams receive a brief physician education in Office-GAP tool use and communication skills.

Educational tool literacy standards: Office-GAP has been rigorously adapted for use with low health literacy patients. All study materials are grade 6 reading level.

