### Outcomes {12}

All data will be collected at baseline, 6 months, and 12 months (Table 2). Our primary outcome is medication adherence measured using eCAP electronic monitoring and self-report. Secondary outcomes are (a) diabetes-specific 5-year CVD risk as measured with UK Prospective Diabetes Study (UKPDS) Engine score; (b) provider engagement as measured by CollaboRATE Shared-Decision Making measure; and (c) patient activation measures (PAM).

**Table 2 Tab2:** Measures table

Variables	Instruments	Methods	Analysis	Time
**Knowledge and attitude about patient-centered care, SDM, use of DSTs**	**Pre and post survey of providers** **Semi-structured interviews**	**90 min. CME interactive orientation sections with providers and exit interviews**	**Descriptive pre-post analysis** **Thematic analysis of transcribed interviews using Dedoose**	**Pre and post physician education** **End of study**
**Medication adherence**	**Medication Events Monitoring Systems ( eCap).** **Cronbach’s alpha=.0.85** **ARMS Survey**	**eCap upload to BRIC** **RA will administer form to patient pre/post intervention to evaluate treatment medication adherence**	**Linear or generalized linear mixed effects model and Beta regression to evaluate changes over time for groups 1 and 2**	**Baseline, 6 and 12 months**
**Patient Activation Measure Scores/Level**	**Patient Activation Measure (PAM) Cronbach’s alpha=.91**	**RA administers form to patient pre and post intervention**	**Linear or generalized linear mixed effects model for change overtime for groups 1 and 2**	**Baseline, 6 and 12 months**
**Self-Efficacy Scores**	**Stanford 6-Item Self Efficacy Scale** **Summary DM Self-Activities Measure (SDSCA)**	**RA administers form to patient pre and post intervention to evaluate change in self-efficacy**	**Linear or generalized linear mixed effects models for change over time for groups 1 and 2**	**Baseline, 6 and 12 months**
**Rate of use of aspirin/antiplatelets, beta-blockers, ACEI/ARBs, cholesterol assessment and treatment, DM medications**	**PAI agreement in chart** **Patient medication list** **Patient medical record** **Texting log**	**Chart audits to compare the rate of use of aspirin/antiplatelets, beta-blockers, ACEI, cholesterol assessment and treatment of DM**	**Linear or generalized linear mixed effects model for change overtime for groups 1 and 2**	**Baseline, 6 and 12 months**

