### Data management {19}

This study is using the Research Electronic Data Capture (REDCap) system for data entry, coding, security, and storage. Data will be entered by using electronic data capture forms, which will be created by the Biomedical Research Informatics Core (BRIC) from paper forms provided by the PI. The BRIC Data Manager will utilize standard quality assessment features within REDCap to monitor ongoing data quality: e.g., missing data for key variables, distribution of variable values, completeness of form data entry, etc. BRIC will design and deploy a programmatic utility to process eCAP data: downloading cloud data, cleaning, analytical structuring, and “number of days adherence” variable derivation. BRIC will maintain secure storage and backup of the downloaded eCAP data.

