### Confidentiality {27}

The procedures for obtaining research material for the study include anthropometric and BP measurements, laboratory data (e.g., glycosylated hemoglobin {HbA1c}), medical records, interviews, and self-completed questionnaires. Research Assistants (RAs) that are trained and certified will obtain all data according to detailed study protocols. Data will be collected directly from enrolled study participants and medical records and used specifically for research purposes. Baseline data will be obtained during group visits only after the patient has signed the informed consent and the HIPAA form. Follow up data will be obtained at 0–1, 3, 6, 9, and 12 months after office visits with their providers. Only individuals officially assigned to the study team or data management team will have access to individually identifiable information about human subjects. This will include the PI, co-investigators, project coordinator, statistician, and research assistants. All individuals will have completed MSU’s IRB human subjects training and will be included on a staff listing of the MSU IRB. Patient survey information, initially collected using paper forms, will be entered into the REDCap database; EMR data will be abstracted using paper forms and later entered into the REDCap database by RAs; eCAP data will be uploaded into eCAP-Provider cloud storage by RAs and then securely downloaded by the BRIC Data Manager to a secure BRIC server.

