## Oversight and monitoring

### Composition of the coordinating center and trial steering committee {5d}

This is a multi-center study designed, implemented, and coordinated across 3 regions in the Midwest, USA.

Principle Investigator: supervises and oversees all aspects of the project.

Project Manager: responsible for day-to-day management of study sites, research assistants, and annual reports.

Research assistants: will recruit participants, conduct group visits and follow-up visits, train, and provide technical assistance to participants with the mobile phone platform Way to Health (W2H).

Biomedical Research Informatics Core (BRIC): organizes data collection and safeguards quality and data.

Research team: meets weekly.

There is no trial steering committee or stakeholder and public involvement group.

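### No researcher is blinded, for a reason that covers only patients and providers, and drug use is audited from sources that differ between the arms

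*Protocol article*

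**What the plan says.** **Blinding.** Who will be blinded? {17a} explains that "neither trial participants nor the care providers can be blinded to the assignment due to the nature of the intervention", and then adds that "Neither the participants nor the researchers are blinded for this study". No reason is given for data managers, chart abstractors or survey staff.

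**Drug use.** In Table 2 (Outcomes {12}), the row on use of antiplatelets, beta-blockers, ACEI/ARBs, lipid treatment and diabetes drugs names four sources: "PAI agreement in chart", the medication list, the medical record and the texting log. The method is chart audit at baseline, 6 and 12 months, analysed as change over time. Table 1 places completion of the Office-GAP agreement in the group 1 component. Of the checklist, the section on the Office-GAP follow-up visit says "Only group 1 patients will use this checklist during their office visits", and that a copy stays in the patient record.

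**Surveys.** For ARMS, Table 2 says "RA will administer form to patient pre/post intervention to evaluate treatment medication adherence", with similar wording for PAM and for the COMRADE/CollaboRATE row. The research assistants (RAs) also "will recruit participants, conduct group visits and follow-up visits" (section {5d}). Confidentiality {27}, however, lists "self-completed questionnaires" among the data sources.

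**eCap.** Data management {19} gives the informatics core (BRIC) a programmed utility for "downloading cloud data, cleaning, analytical structuring" and derivation of adherence days. Days in hospital or the emergency room leave the denominator on the basis of patient report and chart abstraction (Outcomes {12}).

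**The concern.** An open-label trial can still mask the people who process data, and can still measure both arms in the same way. This protocol drops the first without a reason that fits, and departs from the second for one measure.

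The drug-use audit matters because Office-GAP itself produces documents that name each drug. If those documents feed the audit, better recording in group 1 can be mistaken for a change in use, or a real change can be hidden. Moderators and mediators names provider prescribing at 6 months as a possible mediator, so a measurement difference tied to arm could carry into that analysis too.

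For the surveys, ARMS is the self-report part of the primary outcome, and PAM and CollaboRATE are two of the three secondary outcomes. If the RA who taught a patient about adherence then asks how often doses are missed, the answer may be coloured by who is asking. For eCap, the judgement lies in cleaning and in deciding which days to exclude.

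**Working it through.** The protocol gives no figure for any of these biases, so there is none to reproduce. The check is textual, with a short piece of algebra for direction.

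**1. Does the reason reach the researchers?** It names participants and care providers. BRIC staff neither deliver nor receive the intervention. The reason does not reach them, yet the next sentence leaves all researchers unblinded.

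**2. Are the drug-use sources the same in both arms?**

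| Source | Group 1 | Group 2 |
|---|---|---|
| PAI agreement | yes | no |
| Medication list | yes | yes |
| Medical record | yes, with filed checklists | yes, without |
| Texting log | yes | yes |

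This reads the PAI agreement in Table 2 as the Office-GAP agreement in Table 1, since the protocol describes Office-GAP as the patient activation intervention. One source exists in group 1 only, and a second has different content there.

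**3. Which way would this push the result?** Assume no true effect, so that true use *p* is the same in both arms and constant. Let *m* be the share of users missed by what both arms have in common, and *r_t* the share of those missed users that the group 1 forms recover at time *t*. Assume also that the forms only add users.

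- Group 2 observed: *p*(1 − *m*)
- Group 1 observed: *p*(1 − *m* + *m r_t*)
- Spurious difference in change from baseline: *p m* (*r_t* − *r_0*)

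The sign depends only on *r_t* − *r_0*:

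- The agreement is read only at baseline, where Table 1 places it (*r_0* > 0, *r_t* = 0): negative, against group 1.
- Filed checklists add capture only at follow-up (*r_0* = 0, *r_t* > 0): positive, for group 1.
- Equal recovery at all times: zero.

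With purely assumed values *p* = 0.50 and *m* = 0.10 and full recovery, the three cases give 0.50 × 0.10 × (0 − 1) = −5 points, +5 points and 0. These values only show that the sign is open; they are not an estimate.

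**4. How are the surveys completed?** Table 2 has the RA administering the forms. Table 1 and the section on the group visit have patients completing the questionnaires. Surveys (Table 2) has patients completing CollaboRATE after an encounter. Confidentiality {27} speaks of self-completion and of paper forms, but also lists interviews. The mode is not settled.

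**5. Is eCap processing masked?** RAs upload the files and abstract the medical records. BRIC derives the variable, and the stored data are de-identified (Confidentiality {27}). Removing identity is not the same as removing arm, and {17a} claims no masking of any researcher.

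**The case against.** Several counter-arguments have force.

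- **Drug use.** The PAI form is one of four sources, and the rate of use is neither the primary nor a listed secondary outcome. A reader might infer that drug use is read only from a form that group 1 alone has. Table 2 does not say that.
- **Direction.** A reader might compare the arms at one time point and conclude that recorded use is inflated in group 1 by some number of points. Table 2 plans an analysis of change, so such a cross-section leaves out baseline, and its inputs would all be assumed. The checklist is also not named in that Table 2 row; it enters only through the record in which it is filed.
- **Outcomes in general.** A reader might infer that the trial's outcomes are biased towards Office-GAP. The text does not support this. eCap openings are recorded electronically, HbA1c comes from an analyser and blood pressure from an automated device. The Statistical analysis section names eCap as the adherence assessment.
- **Surveys.** Administering a form may mean no more than handing it out. RAs run group visits in both arms, and allocation was stratified by county with both arms in each. With one RA per area, the same RA probably serves both arms. Patients know their arm, so reporting bias from that knowledge remains whatever the mode.
- **eCap.** Derivation is by program, which limits discretion, and details of masking could sit in an analysis plan that is not shown.

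These points narrow the concern. They do not explain why {17a} excludes all researchers from blinding, and they do not make the drug-use sources equal. An analysis plan could add masking only by departing from what {17a} now states.

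**Conclusion.** The point holds in a limited form.

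- The absence of researcher blinding is stated with a reason that does not cover researchers.
- Drug use, an additional measure and a possible basis for the prescribing mediator, is ascertained unequally between arms. The size and direction of the resulting bias cannot be determined from the document. This rests on reading the PAI agreement as the Office-GAP agreement of Table 1.
- The mode of ARMS, PAM, COMRADE and CollaboRATE is described inconsistently. Only the part of self-report bias due to the assessor can be avoided, and it cannot be sized.
- eCap recording is not in question. The exposed steps are cleaning, exclusion of hospital and emergency-room days, and derivation of adherence days.

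**What to change.** 1. **Drug use (Table 2).** In both arms, take the rate of use only from the medication list and the medical record. Exclude the PAI agreement and any filed checklist, and instruct abstractors to pass over those forms. Keep them for fidelity and uptake. An abstractor may still see a filed checklist, so the rule must say that it is not a source.
2. **Blinding ({17a}).** Limit the statement of no blinding to participants, providers and the RAs who deliver sessions. State that BRIC performs eCap cleaning, exclusion of hospital and emergency-room days and derivation of adherence days without arm labels. The statistician generated the allocation (Implementation {16c}) and cannot be fully masked, so the masking belongs at the BRIC step. RAs who abstract the hospital days will still know the arm.
3. **Surveys (Table 2 and Confidentiality {27}).** State in one place that patients complete ARMS, PAM, CollaboRATE and COMRADE themselves, with RA help limited to reading. The eligibility criteria already require a grade 6 reading level.

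The cost is protocol wording and a masked export, with no extra staff. Expect a few more skipped survey items and slightly lower capture of non-prescription drugs, the latter now equal in both arms.
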